### Economic evaluation

The economic questions being addressed in this study are "given the equivalence in long term morbidity and mortality between immediate delivery and expectant management for women with PPROM, what is the least cost alternative from the viewpoint of a health care funder"? and "what are the (utility-based) preferences of women with PPROM for their clinical management"? A cost analysis will be conducted in accordance with the methods outlined by Drummond et al 1997 [30]. This will involve an initial analysis on what resource utilization data can be collected on the patient case report forms, from patient medical records and from routine data collection. It is likely that the biggest drivers of cost will be the number of days admitted to hospital, particularly neonatal intensive care. The methodology for hospital cost will include micro-costing (where differences in resource utilization between patient groups are likely to be important to the final results) and components of case mix cost weights (where utilization is more likely to be similar within patient groups).

Discrete choice methods will be used to establish maternal preferences, using established methods [31]. We will generate a questionnaire based on pair-wise choices similar to the example shown in Table 2. The questionnaire will be administered in face-to-face interviews with a sample of women enrolled in the PPROMT trial. A deterministic sensitivity analysis will be employed where individual parameters are varied one at a time. A random effects probit regression analysis will be used to analyse patient responses to the discrete choice survey, identifying which attributes are important, and the trade-offs between attributes that women are prepared to make.

**Table 2 T2:** Example of a discrete choice question with pair-wise choices

	**Early planned birth**	**Wait for labour**
Time in hospital prior to giving birth	No time	2 weeks
Likelihood of spontaneous vaginal birth	X%	Y%
Time mother spends in hospital after giving birth	1 week	3 weeks
Time baby spends in neonatal intensive car	2 weeks	No time
Which would you choose? (Please circle one only)	Early planned birth or Wait for labour	

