### Fetal and neonatal risks at 34–37 weeks gestation

Clinical decision-making requires consideration of the potential risks and benefits of induction of labour against expectant management with delivery at term or when complications such as chorioamnionitis intervene necessitating delivery. The aim of such management is to maximise the benefits of fetal maturity while avoiding the potential harms of remaining in utero. At gestations between 34 and 37 weeks, whilst the neonate is potentially at increased risk of respiratory distress, difficulty with thermoregulation and difficulty with breast feeding these risks need to be balanced against the increased incidence of chorioamnionitis associated with expectant management in women with PPROM [2]. Histological evidence of chorioamnionitis is present in up to 50% of women who give birth preterm and is often not associated with clinical symptoms or signs [12]. Chorioamnionitis is a known significant risk factor for the neonate for the development of cerebral palsy [12,13]. It is possible that there are increased risks of long term adverse neurological outcomes in those infants whose mothers are managed expectantly with PPROM by increasing their duration of exposure to often subclinical chorioamnionitis.

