### Resource and cost implications of planned early delivery and expectant management of PPROM

Expectant management may result in prolonged antenatal hospitalization, with antibiotic treatment and regular monitoring, and intensive care of the neonate in the event of sepsis. On the other hand, planned early delivery may necessitate intensive care of the neonate for problems associated with prematurity (eg respiratory distress). While some data are available for the US[18,19] and the UK[20], it is not known whether there are differences in the overall cost of care in the Australian setting. However, it is likely that the biggest drivers of health system costs will be the number of days admitted to hospital, particularly neonatal intensive care.

The trial is designed and sufficiently sized to detect a clinically significant difference in neonatal sepsis. We do not, however, expect differences in mortality or long-term morbidity between planned early delivery and expectant management. In the absence of differences in these final clinical outcomes, optimal treatment decisions will also require information about comparative resource use, and information about the preferences of women with PPROM. The secondary aim of the project is therefore to conduct a cost analysis of planned early delivery versus expectant management of PPROM and to establish the treatment preferences of women with PPROM.

Planned early delivery and expectant management represent very different experiences for the women involved. Currently, the relative importance to women of the attributes (health and non-health outcomes and process attributes) of the treatment alternatives is unknown. Discrete choice methodology takes into account the preferences of the mother and has been previously used to explore preferences in a number of relevant areas including intrapartum care[21], miscarriage[22], labour induction[23] and IVF[24]. Maternal preference is likely to assume more importance in the choice of management (of PPROM) if the long term outcomes of treatment are equivalent.

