### Hypotheses

The primary hypotheses are that early planned delivery of women with PPROM close to term is associated with:

1. less short-term neonatal and maternal morbidity compared with expectant management.

2. fewer economic costs compared with expectant management.

3. no difference in long term morbidity or mortality

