### Statistical issues

#### Sample size

The trial is designed to demonstrate a 50% reduction in proven or probable neonatal sepsis from 5% in those women managed expectantly to 2.5% in those women managed with immediate delivery. This requires a total sample size of 1812 women with 80% power and a significance level of p = 0.05. The estimated neonatal sepsis rate of 5% is based on discussions with neonatologists and is conservative compared with the systematic review (6.2% in control arms, where a 50% reduction would require 1448 women). For women who agree to participate we expect almost complete follow-up on the primary outcomes as these will be obtained from the medical records. This sample size will also have adequate power to demonstrate an increase in the need for ventilatory support from 4% in the expectant arm to 7% in the immediate delivery arm.

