## Discussion

### Outcomes and significance

At gestations remote from term, expectant management is appropriate to allow fetal maturation. When PPROM complicates pregnancies closer to term the risks of prematurity are lower and the risk to the infant of sepsis becomes of greater significance. This trial will provide evidence on the optimal care for women with PPROM close to term (34–37 weeks gestation). If it can be demonstrated that early planned birth in this clinical situation is associated with less maternal and neonatal morbidity this will change current practice. The findings of the study will also have significant resource implications as PPROM close to term is a frequent indication for antenatal admission. The trial allows for a detailed assessment of the costs associated with the care of the neonate from the two different care strategies. Given the null hypothesis of no differences between planned early birth and expectant management in mortality or long-term morbidity, information about preferences will allow women and their clinicians to make optimal treatment choices. Information about both preferences and costs will assist policymakers in deciding if, and how, treatment options are presented to women with PPROM. The results of the economic evaluation are thus expected to improve both clinical decision-making and the management of hospital resources. Therefore, analysis of both the clinical and economic sequelae of immediate birth as opposed to expectant management will enable informed decisions and guidelines to be formulated.

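### No difference in mortality or long-term morbidity is listed as a primary hypothesis and taken as the premise of the least-cost question, but the trial as designed cannot establish it

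*Protocol article*

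**What the plan says.** The proposition appears in the protocol article with four different standings.

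- **Primary hypothesis.** The Hypotheses section opens its list with "The primary hypotheses are that early planned delivery of women with PPROM close to term is associated with", and the third item is "no difference in long term morbidity or mortality".
- **Given fact.** The Economic evaluation section asks for the least-cost alternative "given the equivalence in long term morbidity and mortality between immediate delivery and expectant management for women with PPROM".
- **Expectation.** The section on resource and cost implications says "We do not, however, expect differences in mortality or long-term morbidity between planned early delivery and expectant management".
- **Null hypothesis used as a premise.** Outcomes and significance reasons forward from "Given the null hypothesis of no differences between planned early birth and expectant management in mortality or long-term morbidity" to how women and clinicians should choose.

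The section on fetal and neonatal risks allows for the contrary: "It is possible that there are increased risks of long term adverse neurological outcomes in those infants whose mothers are managed expectantly with PPROM".

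On design, the sample size is for superiority on neonatal sepsis, "from 5% in those women managed expectantly to 2.5% in those women managed with immediate delivery", with 1812 women. The mortality outcome is perinatal mortality. The latest infant measure is a questionnaire completed by the mother at four months corrected age. Data analysis specifies chi-square and t-tests for the secondary outcomes. No equivalence margin is given.

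**The concern.** A hypothesis of no difference needs a stated margin, an outcome that measures the thing in question, and enough information to exclude differences beyond the margin. Here the hypothesis is labelled primary, but one half of it (long-term morbidity) has no outcome, and the other half (mortality) has only a test of difference with few expected events.

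The economic question then rests on the proposition. A least-cost comparison is a sufficient basis for choice only if the outcomes held equal really are equal. As worded, no result of the trial could move the question off its premise. A cost ranking could therefore be read as a ranking of the two policies, while the data remained compatible with a material difference in deaths and said nothing about long-term morbidity. The protocol's own review of the evidence asks that further trials report neurodevelopment at childhood follow-up, so the gap is one the protocol itself recognises.

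**Working it through.** **1. The plan's own figure.** Inputs (Sample size): 5% versus 2.5%, 80% power, significance level 0.05, taken as two-sided. Allocation is 1:1. With pooled variance and no continuity correction:

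n per arm = [1.96·√(2·0.0375·0.9625) + 0.8416·√(0.05·0.95 + 0.025·0.975)]² / 0.025² = (0.5266 + 0.2256)² / 0.000625 ≈ 905.4, so 906 per arm and 1812 in total.

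This reproduces the stated number. It is a superiority calculation for sepsis. The protocol gives no calculation for mortality or long-term morbidity.

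**2. Long-term morbidity.** No outcome is collected after the four-month questionnaire. There is nothing to compute: this half of the hypothesis is untested whatever the sample size.

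**3. What was known about mortality.** Table 1 gives perinatal deaths of 2/129 and 2/131, RR 1.24 (0.19 to 8.06). Four deaths do not establish equivalence.

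**4. Precision for mortality with 906 per arm.** The control rate of 2/131 = 1.5% is from Table 1. The rates of 1.0% and 0.5% are assumptions. With the same observed rate p in both arms:

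- SE(log RR) = √(2(1−p)/(906p)). At 1.5%: √(1.97/13.59) = 0.381, and exp(±1.96·0.381) gives 0.47 to 2.11.
- Half-width for the risk difference = 1.96·√(2p(1−p)/906). At 1.5%: 1.96·0.00571 = 1.12 points.

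**5. Power of the planned kind of test at 1.5%.** Using the formula in step 1 solved for power: for a doubling (1.5% to 3.0%), Φ[(0.015·√906 − 1.96·√(2·0.0225·0.9775)) / √(0.014775 + 0.0291)] = Φ(0.193) ≈ 58%. For a halving, about 33%. A true doubling would be missed about 42% of the time and a halving about 67%.

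**6. Could equivalence be shown for mortality?** The protocol gives no margin, so ±1 percentage point is assumed for illustration. Two one-sided 5% tests, true difference zero: power = 2Φ(0.01/SE − 1.645) − 1.

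- At 1.5%: 2Φ(1.751 − 1.645) − 1 ≈ 8%.
- At 0.5%: SE = √(2·0.005·0.995/906) = 0.00331, and 2Φ(3.017 − 1.645) − 1 ≈ 83%.

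| Mortality per arm | Expected deaths per arm | 95% CI for RR at equal rates | Risk difference, ± points | Power to detect a doubling | Equivalence power, ±1 point |
|---|---|---|---|---|---|
| 1.5% (Table 1) | 13.6 | 0.47 to 2.11 | 1.12 | 58% | 8% |
| 1.0% (assumed) | 9.1 | 0.40 to 2.50 | 0.92 | 42% | 38% |
| 0.5% (assumed) | 4.5 | 0.27 to 3.67 | 0.65 | 23% | 83% |

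With one-sided 2.5% tests the equivalence power is 0% at 1.5% and 71% at 0.5%. These are normal approximations and are rough where only four or five deaths are expected. At 0.5%, a 1-point margin is twice the event rate.

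**The case against.** The best defence is that the premise is a working assumption in a secondary aim. The section on resource and cost implications speaks of an expectation and then of a conditional, should final outcomes not differ. The Discussion commits to considering clinical and economic consequences together. Sepsis, ventilation and death are all reported outcomes, so a reader will see costs beside them. An analysis plan not shown here could also add a margin. Much of this stands, and it limits the point. It does not remove it: an analysis plan cannot supply follow-up that is not collected, and the Hypotheses and Economic evaluation sections state the proposition as a primary hypothesis and as a given.

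Five stronger readings are tempting but not supported.

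- *A non-significant mortality test will be reported as equivalence.* No section says so. The Economic evaluation section states a premise before any data, not a conclusion to be drawn from a test.
- *The least-cost comparison fails as soon as sepsis or ventilation differs.* The premise covers only mortality and long-term morbidity. A short-term difference does not contradict it, and the protocol intends to count neonatal intensive care as a cost.
- *The trial can say nothing about equivalence in mortality.* That depends on the death rate and margin, as the last column of the table shows.
- *The background asserts the opposite of the premise.* It says only that harm is possible. That is a tension, not a contrary claim.
- *Sampling error in costs is ignored.* The sentence "A deterministic sensitivity analysis will be employed where individual parameters are varied one at a time" sits in the discrete-choice paragraph, so its bearing on patient-level costs is unclear, and an article may leave further uncertainty methods to a fuller document.

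**Conclusion.** The point holds in a limited form. The protocol gives one proposition four incompatible standings, two of which (primary hypothesis and given fact) the design cannot support. For long-term morbidity the failure is complete, because nothing is measured after about four months. For perinatal mortality it is a matter of precision: at the protocol's 1.5%, equal observed rates would still leave a halving or a doubling of risk inside the 95% CI. If deaths are rarer, the relative interval widens while a wide absolute margin becomes attainable. The 1.5% rests on few deaths; the lower rates and the 1-point margin are assumptions.

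This should be fixed, but it is not critical. The sepsis outcome, its sample size and its analysis are unaffected, and the economic evaluation is a secondary aim.

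**What to change.** 1. Remove item 3 from the primary hypotheses. If the idea is kept, describe it as an expectation, in line with the section on resource and cost implications.
2. State that perinatal mortality and four-month infant development will be reported as estimates of the difference with 95% CIs, with no claim of equivalence.
3. Reword the cost question so that equal long-term morbidity and mortality is named as an untested assumption, and align the Discussion sentence with this.
4. Present the cost difference beside the differences in sepsis, ventilation and death instead of as a stand-alone least-cost conclusion.

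The cost is rewording and a joint presentation of data already planned. The downside is that a pure cost-minimisation conclusion is no longer available.

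Keeping the hypothesis would be far more expensive. It would need a prespecified margin, long-term follow-up and many more women. For mortality alone at 1.5%, with an assumed ±1-point margin, one-sided 2.5% tests and 80% power, n per arm = 2·0.015·0.985·(1.96 + 1.2816)²/0.01² ≈ 3105, or about 6210 in total.

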### Statistical issues

#### Sample size

The trial is designed to demonstrate a 50% reduction in proven or probable neonatal sepsis from 5% in those women managed expectantly to 2.5% in those women managed with immediate delivery. This requires a total sample size of 1812 women with 80% power and a significance level of p = 0.05. The estimated neonatal sepsis rate of 5% is based on discussions with neonatologists and is conservative compared with the systematic review (6.2% in control arms, where a 50% reduction would require 1448 women). For women who agree to participate we expect almost complete follow-up on the primary outcomes as these will be obtained from the medical records. This sample size will also have adequate power to demonstrate an increase in the need for ventilatory support from 4% in the expectant arm to 7% in the immediate delivery arm.

#### Data analysis

Analyses will be by intention to treat, including withdrawals and losses to follow-up. Study groups will be compared in terms of baseline characteristics. As this is a randomised trial, we would anticipate minimal differences in baseline characteristics. If however, important differences are found, these potential confounders will be adjusted for in the analysis of outcomes. For the primary outcome, the relative risk (and 95% confidence interval) of neonatal sepsis in the early planned delivery group compared with the expectant group will be calculated. If adjustment for confounding is necessary logistic regression will be used. The secondary outcomes will be compared using chi-square tests of significance for categorical data and t-tests for continuous data. If adjustment for confounding is necessary logistic regression and multiple linear regression will be used respectively.

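### Covariate adjustment depends on observed baseline imbalance, and the text does not say which estimate, on which scale, is primary once adjustment is triggered

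*Protocol article*

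**What the plan says.** All of the relevant analysis text is in the Data analysis section of the protocol article. The groups are first compared at baseline, with the remark that "As this is a randomised trial, we would anticipate minimal differences in baseline characteristics". The rule then follows: "If however, important differences are found, these potential confounders will be adjusted for in the analysis of outcomes". The section does not say how large a difference must be to count, which variables are candidates, or when the decision is taken relative to sight of the outcomes.

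The main result is specified as follows: "the relative risk (and 95% confidence interval) of neonatal sepsis in the early planned delivery group compared with the expectant group will be calculated". The adjusted alternative is given in one sentence: "If adjustment for confounding is necessary logistic regression will be used". Secondary outcomes follow the same pattern: chi-square tests and t-tests by default, with logistic or multiple linear regression if adjustment is thought necessary.

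The section on procedures and randomisation says that allocation is 1:1 in variable blocks, stratified by centre. Centre is not mentioned in the analysis.

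**The concern.** After proper randomisation, a baseline difference between the arms is a chance event. What justifies including a covariate is how well it predicts the outcome, and that can be judged before any data are seen. A rule driven by imbalance has two consequences.

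- A strongly prognostic variable is left out whenever it happens to be balanced, which is the usual case, and the precision it would have brought is lost. Gestational age is the obvious example. Women enter between 34 weeks and 36 weeks 6 days, and the Background itself says that the risks of immaturity fall as gestation advances.
- With no threshold and no list, the form of the final model is open to judgement after the baseline data are in.

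The second issue is scale. A relative risk is planned, while logistic regression gives an odds ratio unless a further step is taken. No further step is described, and the text does not say whether the unadjusted relative risk or the adjusted result leads the report.

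**Working it through.** **Reproducing the design.** Inputs from the Sample size section: sepsis falling "from 5% in those women managed expectantly to 2.5% in those women managed with immediate delivery", 80% power, alpha 0.05 (taken as two-sided). The pooled-variance formula without continuity correction is

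n per arm = [1.960·√(2·p̄(1−p̄)) + 0.842·√(p0(1−p0) + p1(1−p1))]² / (p0−p1)².

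With p0 = 0.05, p1 = 0.025 and p̄ = 0.0375 this gives 905.4, so 906 per arm and 1812 in total, as stated. With 6.2% and 3.1% it gives 723.1, so 724 per arm and 1448, also as stated. Nothing below alters either figure.

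**How often chance would trigger adjustment.** Assume that the threshold is p<0.05 and that there are k independent covariates (the document gives neither). The probability of at least one trigger is 1 − 0.95^k: 23% for k = 5, 40% for k = 10 and 64% for k = 20.

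**Scale.** OR = [p1/(1−p1)] / [p0/(1−p0)].
- Sepsis, 2.5% v 5%: RR 0.50; OR = (0.025/0.975)/(0.05/0.95) = 0.487.
- Sepsis, 3.1% v 6.2%: RR 0.50; OR 0.484.
- Chorioamnionitis, counts in the article's Table 1 (8/129 v 31/131): crude RR = 0.062/0.237 = 0.26; OR = (8/121)/(31/100) = 0.21.

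The gap is negligible for sepsis and visible for a common outcome.

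**Primary outcome: error rate and power.** Simulations used 906 per arm, 5% control risk, one normal covariate with an assumed odds ratio of 1.5, 2 or 3 per SD, and a p<0.05 trigger (4,000 runs per scenario).
- Type I error with the rule followed mechanically: 4.5–5.5%, the same as unadjusted (4.6–5.5%). With 5 or 10 binary covariates (ORs 1.5–2.0) it was 4.0–5.0%.
- Power at the design effect, rule v always adjusting: 80.3% v 80.8%, 81.4% v 82.4%, 80.8% v 83.2%. A repeat with 6,000 runs gave losses of 0.1, 0.9 and 2.1 points. The loss is therefore roughly 0.5 to 2 points.

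**Continuous secondary outcomes.** Let R² be the share of outcome variance explained by the covariate, and z its standardised baseline difference. Relative to the unadjusted analysis, always adjusting has variance 1−R². Under the rule, the covariate's contribution remains whenever |z|<1.96, so the variance is (1−R²) + R²·E[z²; |z|<1.96].

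Here E[z²; |z|<1.96] = 0.95 − 2(1.96)(0.0584) = 0.721, so the excess over always adjusting is 0.721·R²/(1−R²):
- R² = 10%: 0.721 × 0.111 = 8%
- R² = 25%: 0.721 × 0.333 = 24%
- R² = 40%: 0.721 × 0.667 = 48%

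Simulation gave about 22% and 50% for the last two, which agrees closely. The R² values are assumptions; the document gives none.

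**The case against.** A reader might infer that the rule inflates the type I error, perhaps to 6–9%. Figures of that size need a continuous outcome with a strong covariate, and an analyst who reports whichever of the adjusted and unadjusted results looks better. The text does not authorise that: the trigger is baseline difference, not outcome results. Even if someone did pick the better result, the simulated error for the rare sepsis outcome is about 5–6%. Classification of sepsis is also protected, because the adjudication committee is unaware of allocation. The inflation claim therefore does not stand.

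A reader might also infer that the primary measure becomes an odds ratio. The text does not say so. The relative risk is to be calculated without condition, and a standardised relative risk can be obtained from a logistic model. What stands is that the document leaves the choice open.

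It is also fair to say that adjustment does not shrink the standard error of a log odds ratio as it does for a mean difference. For sepsis the benefit of adjusting is only a small gain in power.

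Finally, covariate lists and model details often belong in an analysis plan, which is not shown here. That would answer a complaint about silence. But the article states a rule, and an analysis plan that followed it would carry the weakness forward.

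**Conclusion.** The point holds as one of pre-specification and efficiency. Observed imbalance is not a sound trigger for adjustment, the trigger is undefined, and the text does not settle which estimate is primary, or on which scale, once it is met.

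For the primary outcome the consequences are small: no inflation of type I error if the rule is followed, about 0.5 to 2 points of power (assumed covariate odds ratios of 1.5 to 3 per SD, p<0.05 trigger), and 0.50 against 0.487 on the two scales. The larger cost falls on continuous secondary outcomes such as length of stay, and only if gestational age is strongly prognostic: 8%, 24% or 48% excess variance at the assumed R² values. For common binary outcomes the two scales differ enough to matter in interpretation, as the chorioamnionitis counts show. The sample size calculation is unaffected.

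**What to change.** - Delete the imbalance trigger and treat the baseline table as descriptive.
- Before unblinding, name a short list of prognostic covariates that are always included: gestational age at randomisation, and centre because it is the stratification factor. At the design rates only about 45 + 23 = 68 sepsis events are expected (906 × 0.05 and 906 × 0.025), so pool small centres or use a stratified method.
- State one primary estimate on the relative-risk scale, from modified Poisson regression with robust standard errors or by standardisation after logistic regression. Use linear regression for continuous outcomes.
- Report the unadjusted relative risk as supportive, and label any adjustment prompted by imbalance as a sensitivity analysis.

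The cost is revised analysis wording and slightly more complex models. Gestational age and centre are known at entry, so no new data are needed, and the total stays at 1812.

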### Setting

The study will be carried out in participating tertiary obstetric, metropolitan and rural hospitals with facilities to manage deliveries at or greater than 34 weeks.

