### Procedures, recruitment, randomisation and collection of baseline data

Eligible women will be identified by a local research co-ordinator and staff. Eligible women will be given the trial information sheet, counselled and encouraged to discuss the trial with her family. Once women have consented to be involved in the trial, their entry details will be recorded on a trial entry form and they will be randomised via a central telephone randomisation service to one of two treatment groups, early planned birth or expectant management.

The randomisation schedule will be prepared by a researcher not involved with treatment allocation. Randomisation will be 1:1, in balanced variable blocks and stratified by centre.

All women will have baseline demographic, past obstetric and medical histories recorded. Maternal temperature will be recorded at a time as close to randomisation as possible. A vaginal swab will be collected from each participating woman and a fetal heart rate tracing obtained. Antibiotic administration is regarded as best practice in women presenting with PPROM and these should be administered in accordance with the policy of the participating centre [25]. At the collaborating centres, data collection will be the responsibility of the local research coordinator.

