#### Expectant management group

In women randomised to expectant management birth will occur after spontaneous labour, at term or when the attending clinician feels that birth is indicated according to usual care.

Care of the all women will be otherwise managed by the obstetric team with care of the infant by the attending neonatologist.

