#### Secondary outcome measures

##### Secondary infant outcomes

will include respiratory distress, perinatal mortality, duration of stay in a neonatal intensive or special care unit, duration of stay in hospital, birth weight, Apgar score at 5 minutes, any assisted ventilation, early infant development as measured by the women at four months (corrected age) using the ages for stages questionnaire [26].

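### Randomisation is stratified by centre but the planned arm comparisons leave centre out: negligible for sepsis, some lost precision for length of stay if centres differ

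*Protocol article*

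**What the plan says.** On allocation, the section on procedures, recruitment and randomisation states: "Randomisation will be 1:1, in balanced variable blocks and stratified by centre". The Setting section names "participating tertiary obstetric, metropolitan and rural hospitals" as the sites. The number of centres is not given.

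On analysis, the Data analysis section says of the primary outcome that "the relative risk (and 95% confidence interval) of neonatal sepsis in the early planned delivery group compared with the expectant group will be calculated". For the others: "The secondary outcomes will be compared using chi-square tests of significance for categorical data and t-tests for continuous data". Adjustment is conditional on what the baseline table shows: "If however, important differences are found, these potential confounders will be adjusted for in the analysis of outcomes". Logistic or multiple linear regression is then to be used. Centre is not mentioned anywhere in that section.

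Secondary infant outcomes include "duration of stay in a neonatal intensive or special care unit, duration of stay in hospital", and the mother's time in hospital is a secondary maternal outcome.

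**The concern.** Blocking within centre makes the two arms nearly equal in number at every hospital, so differences between hospitals largely cancel from the arm comparison. The true sampling variance of the treatment difference is then smaller than under simple randomisation. A t-test or chi-square test that leaves centre out still counts the between-centre variation as error. The reported standard error is then larger than the true one.

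The adjustment rule does not repair this. It responds to imbalance, and centre is the one factor that the design keeps balanced. The balance that keeps centre out of the model is also the reason why it should be in.

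The article itself makes centre differences plausible. Hospitals range from tertiary to rural, antibiotics follow each hospital's own policy, and in the expectant arm "birth will occur after spontaneous labour, at term or when the attending clinician feels that birth is indicated according to usual care". What is at stake is precision on stay and other resource-related outcomes. These matter because the secondary aim is a cost analysis, and the article expects hospital days to be the main cost driver.

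**Working it through.** **Plan's own figure.** Inputs from the Sample size section: 5% against 2.5%, 80% power, significance level 0.05 (taken as two-sided). With pooled variance and no continuity correction:

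n per arm = [1.96·√(2 × 0.0375 × 0.9625) + 0.8416·√(0.05 × 0.95 + 0.025 × 0.975)]² / 0.025² = (0.5266 + 0.2256)² / 0.000625 ≈ 905.4, so 906 per arm and 1812 in total.

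This agrees with the article. The same formula at 6.2% against 3.1% gives 724 per arm, or 1448, also as stated. Neither calculation involves centre, and the point below leaves 1812 unchanged.

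**Continuous outcomes, by formula.** Let ICC be the share of outcome variance lying between centres. The article gives no value, so a range is assumed. With 1:1 balance within centres and a constant treatment effect:

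- k = unadjusted SE / true SE = 1/√(1 − ICC)
- actual type I error of a nominal 5% test = 2[1 − Φ(1.96k)]
- power, where a centre-adjusted test has 80% = Φ(1.96 + 0.8416 − 1.96k)

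| ICC (assumed) | k | SE overstated by | Type I error | Power |
|---|---|---|---|---|
| 0.01 | 1.005 | 0.5% | 0.049 | 79.7% |
| 0.05 | 1.026 | 2.6% | 0.044 | 78.5% |
| 0.10 | 1.054 | 5.4% | 0.039 | 76.9% |
| 0.20 | 1.118 | 11.8% | 0.028 | 72.9% |

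For example, at ICC 0.10, 1.96 × 1.0541 = 2.066, and Φ(2.8016 − 2.066) = Φ(0.736) = 0.769.

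**Continuous outcomes, by simulation.** 50 centres of 36 women (assumed), 18 per arm, 4,000 trials per scenario, t-test against a centre-adjusted linear model:

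| ICC | Type I error, t-test | Type I error, adjusted | Power, t-test | Power, adjusted |
|---|---|---|---|---|
| 0.05 | 0.046 | 0.051 | 77.9% | 79.5% |
| 0.10 | 0.042 | 0.049 | 76.9% | 79.8% |
| 0.20 | 0.026 | 0.046 | 72.2% | 79.5% |

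These agree with the formula.

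**Sepsis, by simulation.** Type I error and power for the unadjusted test against a centre-stratified Mantel-Haenszel analysis:

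- 50 equal centres, ICC 0.01 to 0.05, 10,000 trials per scenario: power 80.4% unadjusted against 80.7% to 81.4% stratified. The standard error of the unadjusted log relative risk is within about 2% of its true value.
- 60 unequal centres (assumed), N = 1812: power about 80% against 80% to 81%; type I error 4.2% to 4.9% against 4.5% to 5.3%.
- 60 unequal centres with wide differences (centre SD of 0.8 to 1.2 on the logit scale, assumed): power 77% to 79% against 78% to 80%; type I error 3.9% to 4.3% against 4.3% to 5.1%.

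The gain from stratifying is about one power point or less in most of these. An outcome at 2.5% to 5% is dominated by its own binomial variation.

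**The case against.** The strongest reply is that a journal article condenses the protocol, and how centre enters a model is commonly left to the analysis plan. That has some force for the primary outcome. A reader might infer that the relative risk is declared crude, but the article only leaves centre unmentioned, and a centre-stratified relative risk would satisfy the sentence. The reply is weaker for the secondary outcomes, where the tests are named. It is also weaker for the adjustment rule, which states when covariates enter and would not bring centre in. That is a stated method, not an omitted detail.

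A reader might also infer that the main result is compromised, or that the intervals are wrong whatever the data. The documents support neither. The estimate is unbiased, any error in the tests is on the conservative side, and sepsis, on which the trial is sized, is barely touched. For stay, the size depends on a variance share that the article does not give. At 1% to 5% the overstatement is only 0.5% to 2.6%.

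Two further objections stand as limits. The formula assumes a constant treatment effect. Birth timing in the expectant arm follows local judgement, so the effect on stay could vary by centre; if centres were then treated as random, the standard error could err in the other direction. Stratifying also has a sparse-data cost. With 60 centres (assumed), each has about 1812/60 ≈ 30 women and 30 × 0.0375 ≈ 1.1 sepsis events. About a third of equal-sized centres (0.9625³⁰ ≈ 0.32) would have none and would add nothing to a Mantel-Haenszel relative risk.

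**Conclusion.** The mismatch is in the text: the design stratifies by centre, the named comparisons leave it out, and the imbalance rule would not add it. The consequence is lost efficiency, not bias or false positives. It is negligible for sepsis. For continuous outcomes it runs from trivial, if centre explains 1% of the variance, to a 12% overstatement of the standard error and about 7 points of power (80% to 73%), if centre explains 20%. These figures assume a treatment effect constant across centres, and the variance shares and numbers of centres are assumptions too. The direction is well founded under that condition; the size cannot be settled from the article. This is an inexpensive improvement, not a defect that threatens the trial's conclusion.

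**What to change.** Amend the Data analysis section so that centre enters the arm comparisons regardless of observed baseline imbalance:

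- **Sepsis and binary secondary outcomes:** Mantel-Haenszel relative risk stratified by centre, with 95% confidence interval. With about 68 sepsis events expected (906 × 0.05 + 906 × 0.025), this is more stable than a logistic model with an indicator for each centre.
- **Continuous secondary outcomes, including stay:** linear regression on treatment with centre as a fixed or random effect.
- **Very small centres:** if any are to be pooled, fix the rule, including a size threshold, before unblinding.
- **Supportive analysis:** keep the unadjusted relative risk.

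The cost is a change of wording. Centre is known for every woman from randomisation, and neither the sample size nor data collection changes.
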